#### Stretching and range of motion exercise

Decreased range-of-motion (ROM) is common in patients with intra-articular hip pain and osteoarthritis (OA) [47]. Muscle stretching exercises will target the hip flexors, hip extensors, abductors and adductor groups to address and maintain hip extension, flexion, adduction/abduction and internal/external rotation. Static and active stretching and foam-roller techniques are employed to emphasise the ROM needed for activities of daily living. Perception skills and dissociation (joint isolation exercises) are trained to allow proper exercise execution and enhance motor control [27–30]. Retraining optimal control of hip abductor muscles, plus stretching for tight flexor muscles may also contribute to a reduction in destructive joint forces and thereby reduce pain [29].

#### Neuromuscular control and functional balance exercise

Proprioceptive deficits routinely occur in conjunction with articular injuries of the hip [48]. Labral injuries lead to an inhibited motor response and decreased neuromuscular stabilisation of the joint [49]. Balance and proprioceptive exercises will be included to restore these deficits and re-establish neuromotor control. Progression is applied by increasing the complexity and difficulty of the exercise, by reducing the base of support, adding dynamic movements on unstable surfaces, and increasing the range through which the movement is performed. Support for neuromuscular training in hip rehabilitation has been reported in the literature [48].

#### Aerobic exercise

Participants will undertake light to moderate aerobic conditioning over the intervention period. In addition to the general health benefits conferred by aerobic exercise, moderate joint loading has been shown to be beneficial for joint health because of mechanosensitive chondroprotective pathways [50]. No study has described the optimal dose of aerobic exercise for patients undergoing hip rehabilitation in terms of intensity, volume and duration [47]. In this study, the supervising physiotherapist will determine the nature of aerobic exercise (walking, cycling, swimming, cross-trainer), and progression in intensity based on individual examination finings and patient response to exercise. In patients with a differential diagnosis of FAI, static cycling will be undertaken with caution and an elevated seat to avoid combined deep hip flexion and internal rotation [13].

### Manual therapy

Manual therapy techniques will be used to modify the quality and range of motion of the hip and associated soft tissue structures, and assist with pain relief. The manual therapy intervention will be prescribed individually for each participant on the basis of the physical examination findings, from a limited list of techniques including trigger point massage, passive joint mobilisation, distraction and sustained stretches. These techniques are informed by evidence-based best practice and are commonly used in the management of hip dysfunction [5, 30, 36]. Lumbar spine mobilisation, in the form of passive accessory intervertebral movements, will be performed in those patients where the physiotherapy assessment identifies a requirement [5].

### Education

Educating the patient on factors surrounding their treatment and the importance of regular exercise could be a key element for patient adherence to a home-based exercise programme [51, 52]. Education and advice will be a focus of the intervention and will include information on diagnosis and aetiology of FAI/hip pain, rationale for treatment, the benefits of exercise, joint protection and activity modification strategies, pain management, coping with acts of daily living (sitting, driving, sleeping, work), and the importance of increasing physical activity levels in everyday life. The contents of the education component will be evidence-based [10, 40] with the overall focus directed towards increasing the knowledge of the participant on issues surrounding their condition.

### Home-based programme

Participants will be instructed to complete an individualised, unsupervised home exercise programme during the 12-week follow-up period. This programme is prescribed by the physiotherapist at the final treatment session. To optimise adherence, the programme will comprise four to six exercises performed three times per week [29, 30, 35]. The selected exercises will reflect the patient’s clinical priorities for treatment determined by the physiotherapist on completion of the supervised phase of the protocol. The home exercise programme will comprise any combination of strengthening, stretching, neuromuscular control and aerobic exercise. The starting level will reflect the participant’s functional capabilities upon commencement of the follow-up training period. Guidance on exercise progression will also be provided, and participants will receive written instructions demonstrating the home exercises. Participants will be asked to report all training sessions in training diaries. Diary records will be used to measure compliance to the home programme. A goal is that participants should complete a minimum of 80 % of the prescribed exercise sessions [50].

### Outcome measures

Outcome measures with proven validity and reliability have been selected based on those recommended for clinical trials of intra-articular FAI [53], and current practice in UK military rehabilitation [54]. Standardised instruments recommended by OMERACT-OARSI guidelines [55] will also be included. These guidelines require measures of pain, physical function and a global assessment of health related quality of life. Participants will be assessed at baseline, on completion of treatment (1-week MDT group; 6-weeks IP group) and 12-weeks follow up (Fig. 1). The follow-up time-frames are the same for both groups (12-weeks), and all participants will be assessed at baseline and 12-weeks on the same clinical outcome measures. The inclusion of post-treatment measures may help reveal if any differences occur as a consequence of the different interventions (e.g., the immediate post-treatment scores by group). All outcome measures will be conducted, administered and overseen by the same supervising therapist on each occasion. Outcome measures used in the study are summarised in Table 4.

**Table 4 Tab4:** Summary of outcome measures

Primary outcome measure^a^	Data collection instrument
Function in daily living	Subscale of HAGOS
Physical function, activity level	Subscale of HAGOS
Hip symptoms, numeric pain rating	Subscale of HAGOS, subscale of NAHS, VAS
Secondary outcome measures^a^	
General health status	EuroQol -5D (EQ-5D-3 L)
Mood, anxiety, depression	HADS
Objective functional performance	6-minute walk test
Hip range of motion	Clinical methods and goniometry
Dynamic balance/postural control	Modified Star Excursion (Y-Balance) Test
Hip muscle strength	Hand held dynamometry
Treatment efficacy & self efficacy	SIRBS
Adherence to home-based exercise	Training Diary and 11-point rating scale
Patient demographics & past treatment	Questionnaire

^a^The primary end-point for data analysis is 3-months. All measures will be taken at baseline, post-treatment (1-week MDT group; 6-weeks IP group), 3-months with the exception of patient demographics which will only be assessed at baseline

*HAGOS* Copenhagen Hip and Groin Outcome Score, *NAHS* non-arthritic hip score, *VAS* visual analogue scale, *HADS* hospital anxiety and depression scale, *SIRBS* sports injury rehabilitation beliefs survey

#### Descriptive data

Personal and demographic characteristics including age, height, body mass, body mass index (BMI), gender, duration of symptoms, previous injuries, previous treatments, medication use, military occupation, duration of military service, smoking and drinking habits, and sporting/exercise participation will be obtained by questionnaire.

The primary outcome measures and instruments will be:
***The Copenhagen Hip and Groin Outcome Score (HAGOS)***. The Copenhagen Hip and Groin Outcome Score (HAGOS) was developed in 2011 and is specifically designed for young to middle-aged, physically active individuals with hip and groin pain [56]. This patient-reported questionnaire is a quantitative measure of hip disability based on the different levels of the International Classification of Functioning, Disability, & Health. The HAGOS contains 37 questions, covering six domains: pain (10 items), symptoms (7 items), physical function in daily living (5 items), physical function in sport and recreation (8 items), participation in physical activities (2 items), and hip and/or groin-related quality of life (5 items). Construct validity and responsiveness to change have been shown with statistically significant correlation coefficients of 0.37 to 0.73 (*P* < 0.01) for convergent construct validity and from 0.56 to 0.69 (*P* < 0.01) for responsiveness [57]. The HAGOS was selected because it is designed to assess changes from week to week induced by physical therapy [58] in a young to middle-aged population approximating the demographic characteristics of our target sample.
***The Non-Arthritic Hip Score (NAHS)***. The non-arthritic hip score (NAHS) comprises 20 questions covering four domains: pain (five items), symptoms (four items), acts of daily living (ADL; five items), and physical activities (six items). The questionnaire was developed for the assessment of hip pain in young participants with increased activity demands [59]. Several questions related to mechanical symptoms and physical activities relevant to active military patients are included. Convergent construct validity has been confirmed with a statistically significant correlation coefficient of 0.82 [57]. The NAHS is currently used within UK military rehabilitation, and scales of this kind are frequently used as an external criterion for comparison with changes in scores of other outcomes [5]. Therefore, the NAHS will be used to assess similarity of results with other self-reported measures included in this study.
***The Visual Analogue Pain Scale***
*.* A visual analogue scale (VAS) will be used to measure pain intensity. The patient will be asked to rate their worst hip/groin pain experienced over the past 24-h using a 100 mm horizontal VAS anchored by the terms ‘no pain’ and ‘worst pain possible’. The supervising physiotherapist will also enquire if the sensation of pain is sharp or a dull ache, and if pain is made worse by movement. The 100-point VAS scoring requires no mathematical transformation, and with a normal distribution of data, it allows for parametric statistical analysis [60]. The VAS response format has shown good internal consistency, is easy to understand, is in wide clinical use, and has been sufficiently evaluated in clinical trials [60, 61].

The secondary outcome measures and instruments will be:
***EuroQuol-5D(EQ-5D-3L)***. The EQ-5D is a standardised, validated questionnaire for the self-rating of a patient’s health status [62]. It comprises a visual analogue scale (VAS) measuring self-rated health and a health status instrument consisting of a three-level response (no problems, some problems and extreme problems) for five domains [63]; (a) mobility, (b) self-care, (c) usual activities, (d) pain and discomfort and (anxiety and depression). A respondents EQ-VAS gives self-rated health on a scale where the endpoints are labelled ‘best imaginable health state’ (100) and ‘worst imaginable health’ (0). The EQ-5D has been shown to provide more exact ratings of everyday activities and their disease-related restrictions compared with other measures of health related quality of life (QOL) [64]. The inherent consistency of the EQ-5D test has been evaluated in the literature and shown good responsiveness to change in patients with hip conditions [65], and has been used in similar populations with similar musculoskeletal complaints to our study population [66].
***Hospital Anxiety and Depression Scale (HADS)***
*.* This self-report questionnaire measures mood disorder and is validated for use as a screening tool in the general population [67]. It contains 14 items, seven relating to anxiety and seven relating to depression, which are scored separately. A score of 0–7 indicates no anxiety or depression, 8–10 is viewed as ‘borderline’ and 11–21 indicates the presence of anxiety or depression [36]. Previous research has demonstrated a link between hip OA and psychological wellbeing [68]. The HADS will be used to identify if anxiety or depression are confounders to treatment response and predictors of treatment outcome.
***6-Minute Walk Test***. Physical performance measures should be used in combination with self-report measures in the assessment of physical function [69]. The 6-minute walk test (6MWT) measures the distance an individual is able to walk over a total of 6 min on a hard, flat surface [70]. The goal is for the individual to walk as far as possible (measured by metres covered) in 6 min. The individual is allowed to self-pace and rest as needed as they traverse back and forth along a marked walkway. Timed walk tests have previously been used as a direct measure of physical performance in exercise-based osteoarthritis trials [36, 71], with positive inter-rater reliability [ICC 0.95 (CI:0.90, 0.98)] reported in one hip OA study [72].
***The Modified Star-Excursion Balance (Y-Balance) Test***. Impaired standing balance has been reported in people with hip pain compared with age matched healthy controls [73], and the exercise intervention in this study aims to correct poor balance and postural control. Dynamic balance and postural control will be measured using the modified star excursion balance test (SEBT), known as the Y-Balance test [74]. The test is performed with the participant standing on one leg and then reaches with the free limb as far as possible along three lines positioned in anterior, posteromedial, and posterolateral directions (Fig. 2). The Y-Balance Test was developed to standardise performance of the SEBT incorporating those directional movements with the greatest accuracy in identifying lower extremity dysfunction [75, 76]. The test has demonstrated good intra-rater reliability with reliability coefficients (ICC 2,1) ranging from 0.67 to 0.96 [62], and is currently used as a measure of postural control in patients undergoing UK military hip pain rehabilitation [54].

**Fig. 2 Fig2:**
[figure not shown]
Y-balance test. From a single-leg stance the participant reaches the freely moveable limb along a line in the **a** anterior, **b** posterolateral, and **c** posteromedial directions
***Hip Range of Motion (HROM)***
*.* Loss of range of motion is a common clinical finding in hip OA and intra-articular hip disorders, and is associated with pain and disability [1, 2, 36, 40]. Passive range of motion will be measured on both sides for hip flexion, abduction and medial rotation using a high precision inclinometer. Individual scores will be recorded and used for analysis purposes. High test-retest reliability values have been reported (0.82, 0.86, and 0.90 respectively using the intra-class correlation co-efficient (ICC)) in subjects with hip OA [36, 77]. Whilst this is a standard assessment commonly employed in the clinical setting, consistency in measurement technique will be confirmed during a 1 day training session at DMRC prior to commencement of the study. A description of testing positions and techniques is provided in Additional file 1.
***Hip Muscle Strength***
*.* Strength assessment plays an important role in the clinical examination of the hip [78, 79]. Muscle strength measurement in this study will be analysed in parallel with the assessment of physical function to establish the contribution changes in muscle strength may have on functional performance. Hip muscle strength will be measured on both sides for flexion (FL), extension (EX), abduction (AB), adduction (AD), internal rotation (IR) and external rotation (ER). Strength measures will be taken using hand-held dynamometry (HHD). Participants will be tested on a clinical examination couch in either a seated or supine position depending on the movement being measured. Test positions were chosen based on procedures often applied in the clinical setting [79–81]. In accordance with the description of Thorborg et al. [78] an isometric ‘make-test’ will be used for testing. This test was chosen as isometric loading induces less stress on the musculoskeletal system than eccentric loading (‘break-test’), which is a key consideration when testing individuals with a physical injury [79]. A long lever arm will be utilised during the six individual tests wherever possible to ensure the tester’s strength exceeds the isometric force applied by the participant. For each movement the examiner will apply resistance in a fixed position whilst the participant exerts a 5-s isometric maximal voluntary contraction (MVC) against the dynamometer and the examiner. Participants will perform four consecutive attempts for each movement with a 30-s recovery between attempts. Strength measures will be reported as Newtons (N). The highest value will be used for analysis purposes. Good interrater reliability (ICC 0.76–0.79) and low test-retest variation (<10 %) has been demonstrated for the HHD measurement technique in measuring hip muscle strength [78, 81]. Descriptions of measurement techniques are provided at appendix 10 in Additional file 1.
***Sports Injury Rehabilitation Beliefs Survey (SIRBS)***
*.* The purpose of the education programme in this study is to empower patients to manage their own pain and to maintain physical function. Perceived self-efficacy is defined as a person’s judgement or belief of their ability to change, manage or execute tasks related to pain [82]. Several studies have found that a patient’s perceived self-efficacy is related to health outcomes and the course of disease progression [82, 83]. The Sports Injury Rehabilitation Beliefs Survey (SIRBS) [84] is a 19-item instrument that contains five subscales assessing severity, susceptibility (threat appraisals), treatment efficacy, and self-efficacy (coping appraisals). Ratings are made on a 7-point Likert-type scale ranging from 1 (very strongly disagree) to 7 (very strongly agree). In this study, only the treatment efficacy (4-items), and self-efficacy (4-items) subscales will be used. Acceptable alpha coefficients have been reported for treatment efficacy (0.85) and self-efficacy (0.91) [85], and low-to-moderate interscale correlations provide some support for its construct validity [84].
***Adherence to Home Exercise***
*.* Low adherence to home based exercise programmes is widely accepted as a key contributor to poor long-term clinical rehabilitation outcomes [85, 86]. To measure adherence during the 3-month follow-up period, participants in this study will be asked to maintain a diary/log-book recording the frequency, duration and intensity of the exercises in their home-based programme. Participants will also rate their adherence to the home programme at 3-months on an 11 point rating scale (with 0 being ‘not at all’ and 10 being ‘completely as instructed’). This method of measuring adherence to home-based exercise has previously been used in hip rehabilitation randomised controlled studies [5, 29].

### Sample size

The primary endpoint will be change from baseline to 12-weeks in (a) the HAGOS ‘physical function in daily living’ subscale and (b) VAS numeric pain rating. Sample size calculation is based on clinically relevant changes over the study period (e.g., score changes between baseline and follow-up should be, on average, subjectively perceptible by the participant). The minimum clinically important difference (MCID) in the HAGOS subscale has been suggested to be 4.8–5.2 points [53]. Between participant standard deviations have not been widely reported for the VAS using intra-articular hip pain patients [1, 10]. Therefore, the required sample using a MCID of 5.2 between groups on the HAGOS subscale and a standard deviation of 11 points, with a significance level of 0.05 (2 tailed) and a power of 80 %, is 43 per group. Allowing for an estimated drop out rate of approximately 15 % at the 12-week follow-up, a total of 100 participants will be recruited into the study. Based on current referral rates it is anticipated this sample target will be met from routine referrals to DMRC Headley Court and no additional strategies to promote enrolment are required. The sample size was calculated using G*Power software Version 3.0.10 (Franz Faul, Universitaet Kiel, Germany). There is currently no RCT reporting the effects of a residential MDT intervention versus outpatient individualised treatment approaching this sample size in the available literature.

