### Randomisation and treatment allocation concealment

A block randomisation method will be used to randomise subjects into groups that result in equal sample sizes. This method will ensure a balance in sample size across both groups over time. Blocks are small and balanced with pre-determined group assignments, which keeps the numbers of subjects in each group similar at all times, whilst ensuring there is a 50:50 likelihood of participants being allocated to either group. Due to the possible influence of gender on the efficacy of strengthening exercise [32, 33], the study will only recruit male participants. After patient eligibility has been confirmed and informed consent obtained, a sealed envelope will be opened to reveal group allocation by an independent administrator not involved in the recruitment, treatment or assessment of study outcomes. A plain language statement will inform participants that they have an equal chance of receiving the residential MDT or individualised outpatient intervention. Group allocation will be documented and communicated to the supervising therapists by the independent administrator. Prior to the study, all treating staff will have received a briefing on the study protocol, the ethical, clinical and scientific basis of the study, the randomisation process and specific intervention for each treatment group, in line with the study protocol. It is not possible, relevant or necessary to blind participants to treatment allocation in this study. The clinical staff supervising both groups will be, by necessity, unblinded. Day and Altman [34] suggest blinding assessment by using non-involved assessors to record outcome scores. This is not possible in our study as independent assessors with specific knowledge of quantification of clinical outcomes are not available due to specialist staff man-power limitations. To minimise the potential influence of outcome assessors, instructions are standardised to ensure consistency in measurement. A medical statistician assisting with statistical analysis will be blind to group allocation until completion of the analysis.

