^2^ test. A significance level of 0.05 will be set for any inferential statistics conducted. The inclusion of the post treatment (T2) measure may help reveal if any differences occur as a consequence of the different interventions (as T2 reflects the immediate post-treatment scores for each group). However, this is based on the assumption that any changes in outcome from T1 and T2 (over 1 and 6-weeks) are linear, and also between T2 and T3. We recognise if the trend is non-linear then we will have insufficient data points to model the outcome over time in a way that will enable us to compare the trajectory of patient outcomes using the 3 time points. If interim analysis reveals this to be the case, we will remove T2 measures from the final analysis.

Secondary analysis will be undertaken to assess the predictors of outcome at the primary endpoint (12 weeks post treatment commencement) in both groups, using multiple regression analysis. Predictor variables including age, gender, baseline pain, physical function, duration of symptoms, mood/anxiety, self-efficacy, co-morbidities and exercise adherence will be measured. Analyses will be performed separately for MDT and IP group treatments. Response variables will be change in HAGOS function in daily living score pre and post intervention (MCID > 5.2 points) and numeric pain rating on the VAS. All predictors will be checked for collinearity. Univariate logistic regression will be performed on all potential predictors and those associated with the outcomes will be entered into the multivariate logistic regression model. Variables with the lowest predictive value will be removed from the model if *p* > 0.05. Odds ratios and 95 % CI’s will be calculated for all final predictors.

No statistical adjustment will be made for multiple testing. All tests will be two-sided and carried out at the 5 % level of significance. Changes to the study design or analysis plan will be documented with full justification. A statistician will oversee the blinded analyses of the data. The statistical analysis procedure will be discussed, reviewed and co-worked with statisticians at the Department for Health University of Bath, and School of Clinical Sciences at Bristol University.

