## Discussion

Hip arthroscopy and non-surgical interventions such as the treatments offered by physiotherapists, are recommended in the management of non-arthritic FAI [1, 9].

However, despite the popularity and acceptance of residential MDT rehabilitation in the UK military, there are no studies presenting empirical data on the structure, process or efficacy of non-arthritic hip pain care. Given the interest in this model across the wider healthcare sector, there is an immediate need to test the efficacy of residential rehabilitation practice in a randomised trial to ensure all future patients receive rehabilitation in the optimal clinical setting.

This paper presents the protocol for a randomised controlled trial that will compare the effects of a residential MDT intervention with conventional outpatient care on pain and physical function in young non-arthritic hip pain patients. The study will be the first RCT to evaluate the structure and process of residential versus outpatient treatment options in young active adults with intra-articular, non-arthritic hip pain. The study design includes methodological elements to minimise the potential for bias including a power calculation, randomisation and intention-to-treat analysis. The primary and secondary outcomes are reliable and valid self-report measures of function and pain, quality of life, and physical capacity tests including dynamic postural control, walking and HROM.

Bennell et al. [5, 28] have previously employed a semi-structured treatment programme similar to the out-patient intervention in our study. These authors highlight that whilst this approach restricts individual tailoring of the programme, it reduces treatment variation thereby ensuring the intervention is accurately reported and replicated. We chose not to include a ‘no treatment’ control arm as natural recovery is unlikely to occur in participants reporting functional impairments and pain at baseline [28], and imposing natural recovery could be considered unethical.

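### The 43 per group in the sample size section does not follow from its stated inputs, which need 71 to 72 per group; unadjusted power at 43 is about 58%, not 80%

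*Protocol article*

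**What the plan says.** The Sample size section of the protocol article names change from baseline to 12 weeks in the HAGOS daily living subscale as a primary endpoint, together with VAS pain. It sizes the trial on the HAGOS subscale only: "required sample using a MCID of 5.2 between groups on the HAGOS subscale and a standard deviation of 11 points", two-tailed 5% significance, "and a power of 80 %, is 43 per group". It puts the minimum important difference at 4.8 to 5.2 points. After an allowance of roughly 15% for dropout, "a total of 100 participants will be recruited into the study". G*Power is named as the software, but the test chosen within it is not.

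Two further statements fix the remaining inputs. The randomisation section sets 1:1 allocation ("randomise subjects into groups that result in equal sample sizes"), and the Statistical analysis section leaves alpha undivided ("No statistical adjustment will be made for multiple testing"). That section plans linear and mixed models with a repeated-measures ANOVA. It gives no correlation between visits and does not link the model to the sample size.

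**The concern.** The section gives everything a two-group comparison of means requires: difference, SD, alpha, sidedness, power and allocation. A reader can therefore recompute the result, and the recomputation does not give 43. The stated figure is about 60% of what the inputs require (43/72 = 0.60).

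The 80% is the only stated justification for the trial's size. In a superiority trial, the reader of a non-significant result needs to know how likely the design was to detect the difference it calls important. On the stated inputs, an unadjusted comparison would miss a true 5.2-point difference about 42% of the time, against the 20% that the text implies.

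**Working it through.** **Inputs.** From Sample size: difference 5.2, SD 11, alpha 0.05 two-sided, power 80%. From the randomisation section: 1:1 allocation. From Statistical analysis: no split of alpha.

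**Attempt to reproduce 43.** For two means, n per group = 2 × (z₀.₉₇₅ + z₀.₈₀)² × (SD/difference)².
- (1.960 + 0.842)² = 7.851
- (11/5.2)² = 4.475
- n = 2 × 7.851 × 4.475 = 70.3, so 71 per group

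The noncentral t calculation gives 71.2, so 72 per group. The stated 43 is not reproduced.

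**Variants on the same inputs (t-based).**

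| Reading | n per group |
|---|---|
| Two-sided, 5.2 points | 72 |
| One-sided, 5.2 points | 57 |
| Two-sided, 4.8 points | 84 |
| One-sample or paired, two-sided, 5.2 points | 38 in total |
| One-sample or paired, two-sided, 4.8 points | 44 in total |

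None gives 43. The last row comes close, but it is a within-group calculation and does not use the stated 5.2.

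**Power for 5.2 points, SD 11, unadjusted (noncentral t).**
- 43 per group: 58.2%
- 42.5 per group (100 less 15%): 57.7%
- 50 per group: 64.8%

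**What 43 per group would support at 80% power.** Either a difference of 6.72 points with SD 11, or an SD of 8.51 with a difference of 5.2.

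**Could baseline adjustment explain 43?** The required variance ratio is 43/71.2 = 0.604. The answer depends on what the SD of 11 describes, which the article does not say. Here r is the correlation between baseline and 12 weeks.
- If 11 is a single-visit SD, ANCOVA multiplies the variance by 1 − r². Then 1 − r² = 0.604 gives r = 0.63.
- If 11 is the SD of change, ANCOVA multiplies the variance of change by (1 + r)/2. Then (1 + r)/2 = 0.604 gives r = 0.21, and larger r makes matters worse.

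| r | ANCOVA power at 43 per group, single-visit SD | ANCOVA power at 43 per group, change SD |
|---|---|---|
| 0.3 | 62% | 77% |
| 0.5 | 71% | 71% |
| 0.6 | 77% | 68% |
| 0.7 | 86% | 65% |

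The two columns run in opposite directions, so no single correlation can be put forward as the one the design needs until the SD is defined. An unadjusted change-score analysis with a single-visit SD of 11 would need r of about 0.70. If 11 is already the SD of change, that analysis gains nothing and stays at 58%.

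**Could a repeated-measures test explain 43?** A between-group repeated-measures F test gives 44 per group with two measurements at a correlation of 0.2, or with three at 0.4. That comes close, but it rests on a correlation the article does not state. It also tests the group difference averaged over visits, not change to 12 weeks.

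**The case against.** The strongest reply is that the trial will not be analysed by an unadjusted t-test. The planned analysis is a repeated-measures mixed model, chosen because it handles within-participant correlation, and G*Power offers repeated-measures options that come close to 43. On this view an input was left out in condensing the protocol, and the calculation itself may be sound.

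Part of this stands. An omitted correlation is a live explanation alongside a plain miscalculation, and the document cannot tell them apart. It also follows that a reader might infer that the trial's actual power is 58%. The documents do not support that: 58% belongs to an unadjusted comparison on the stated inputs, and power under the planned model may be higher.

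The reply does not rescue the sentence as written. It presents its inputs as yielding 43, and they yield 71 to 72. No correlation, covariate or repeated-measures gain is mentioned. The Statistical analysis section also allows the post-treatment measurement to be dropped from the final analysis, so a gain from three visits cannot be relied on.

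A reader might also infer that the dropout step is wrong, since 43/0.85 = 50.6, or 51 per group. That is not supported either. The rate is given only as approximate, 43 × 1.15 = 49.5 rounds to 50, and keeping 86 of 100 is a 14% loss. The recruitment total is consistent with 43.

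**Conclusion.** The figure of 43 per group is wrong as stated. The inputs given require 71 (normal) or 72 (t-test) evaluable participants per group. For an unadjusted comparison, power for 5.2 points is about 58% with 43 per group and about 65% with no losses from 50. The difference detectable with 80% power at 43 per group is about 6.7 points, outside the quoted 4.8 to 5.2 range.

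These figures assume a two-sided 5% test, equal groups and an SD of 11 for the quantity being compared. Power under the planned repeated-measures model cannot be determined from the article.

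**What to change.** Keep 100 participants and correct the statement: about 58% power for 5.2 points, or 80% power for about 6.7 points, for an unadjusted comparison with SD 11 and 43 per group analysed.

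If a baseline-adjusted or repeated-measures calculation was actually used, report it in full: the test selected, the correlation, the source of that correlation, and whether 11 is a single-visit SD or the SD of change. The correlation should come from that source and not be chosen to return 43. As a check, 80% power with ANCOVA at 43 per group needs r of about 0.63 or higher for a single-visit SD, or about 0.2 or lower for a change SD.

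The cost is a change of wording and a less favourable power statement, with no extra participants. For comparison, achieving 80% unadjusted power for 5.2 points with 15% dropout would take 71/0.85 to 72/0.85, or 84 to 85 per group: 168 to 170 in total. The dropout step needs no change.
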